### The Interventions

The intervention to be evaluated consists of two integrated but distinct programs. The first program is for parents, "My child and the accident: A story with a good ending" [29] and the second program is for children/adolescents, "Me and the accident: A story with a good ending" [30]. Participants in the '*family-focused' *intervention will receive *both *the child and parent program whereas participants in the *'child-focused' *intervention condition will receive *only *the child program.

These programs were developed and piloted as part of a research project conducted by two of the authors (VC & JK). In both treatment conditions, participants will be seen by a psychologist individually. All sessions in both treatment programs are of approximately 1.5 hours in duration. In the family-focused intervention condition, the parent and child programs will be delivered consecutively, with parents completing parent sessions first. The parent program consists of four sessions and aims to: provide psychoeducation about PTSD, as well as a rationale for the child program; focus on danger perceptions and the way these change after a traumatic incident (with an emphasis on factors such as the possible communication of threat from parent to child and reinforcement of perceptions of danger); focus on changes in parenting practices after a traumatic incident affects a family member and encourage parents to think about their own parenting behaviours and whether these are likely to be helpful or not; and support parents to develop the skills to effectively parent a child experiencing PTSD.

The child/adolescent program consists of six sessions. This program takes a strengths-based, resilience-building approach; is age appropriate, incorporates creative drawing and writing tasks and aims to: provide psychoeducation about the role of thoughts, behaviours (avoidance) & physical reactions in anxiety (and in PTSD in particular); emphasize the importance of the young person's story of his/her accident and their perceptions of current danger or threat; assist children/adolescents in identifying the 'hot spot' thoughts (i.e., particularly emotive thoughts or images) in their story; provide young people with the skills to challenge their hot spot thoughts and to manage their "intruder thoughts" (i.e., any intrusive thoughts or images experienced); and plan for the future (relapse prevention).

### Participants, Recruitment & Inclusion/Exclusion Criteria

Participants will include children and adolescents aged between 7 and 16 years (and their parents). Children who have presented to either the Emergency Department of the hospital wards following an accidental injury (e.g. sporting injury, burns, MVA) will be eligible for inclusion. A complete list of inclusion/exclusion criteria is given in Table 2.

**Table 2 T2:** Inclusion/Exclusion Criteria

Inclusion Criteria	Exclusion Criteria
Aged between 7 and 16 years	Parent's English insufficient for questionnaire completion
Admission to hospital for a minimum of 6 hours for accidental injury	Developmental delay or mental retardation in the child
Endorsement of CTSQ items indicating 'at risk' status within 2 weeks of admission	Moderate to severe head injury or posttraumatic amnesia following the accident
Elevated clinical symptoms defined by meeting PTSD-AA or DSM-IV criteria on the structured diagnostic interview (Clinician-administered PTSD Scale for Children and Adolescents: CAPS-CA; Nader et al.)	Alcohol or substance abuse, or psychosis in the caregiver
Consent to participate in the study	Severe depression or suicide risk in the child
Family must live within 200 km's or be willing to travel for weekly therapy sessions	Child currently under the care of Department of Child Safety
	Injury due to physical or sexual abuse (intentional injury)

Recruitment procedures will be identical across the three hospital sites and will involve several stages.

#### Stage 1 - Participant identification

Within each hospital's Emergency, Medical and Surgical wards, Research Nurses or Research Assistants will identify eligible participants according to inclusion/exclusion criteria. Eligible families will be contacted while still in the hospital and given an Information Sheet and a "Consent to Contact" form.

#### Stage 2 - Screening

Eligible families who have given their permission to be contacted will be contacted either by phone (or in person if the child/adolescent is still in hospital) 1-2 weeks after their initial admission to the hospital. If the family remains interested in participating in the study, consent and assent forms will be completed and the Child Trauma Screening Questionnaire [CTSQ: [10]], a brief 10-item self-report screen, will be administered to the child/adolescent by a trained Research Assistant. Administration of the CTSQ may occur either over the telephone or at the hospital, depending on whether the young person has been discharged. Children/adolescents scoring above the cut-off score (>5) on the CTSQ will be judged to be 'at risk' for developing PTSD and will be invited to proceed to Stage 3.

#### Stage 3 - Diagnostic assessment

At approximately 4-6 weeks following the young person's initial admission to the hospital, those participants judged to be at risk for PTSD will undergo a face-to-face diagnostic assessment. At this time, a diagnostic interview, the Clinician Administered PTSD Scale - Child and Adolescent Version [CAPS-CA; [31]] will be conducted by a trained Research Assistant with children/adolescents. If the participant meets diagnostic criteria for either full or partial PTSD, the measures outlined in Table 1 will be administered to children/adolescents and parents. In order to proceed past this stage, children/adolescents must meet at least 2 out of the 3 cluster criterions for PTSD on the CAPS-CA. In other words, they must meet either full or partial diagnostic criteria for PTSD.

#### Stage 4 - Intervention

Participants who fulfill either full or partial diagnostic criteria for PTSD and agree to participate in the study will be randomly assigned to either the waitlist condition (WLC) or one of the two active treatment conditions; child-focused cognitive-behavioural therapy (CF-CBT) or family-focused cognitive-behavioural therapy (FF-CBT). Participants in the WLC will be randomly assigned to one of the two active treatment conditions after 10 weeks of having been in the WLC (following a re-assessment at this time).

#### Stage 5 - 4-week post-baseline assessment

Participants in the FF-CBT condition will complete the parent program in the first four weeks, and to evaluate changes in parent and child behaviours over this time, a brief assessment will be conducted following the completion of parent sessions, or at 4-weeks post-baseline assessment. To enable a comparison to participants in the CF-CBT and WLC groups, all participants will complete this assessment at 4-weeks post-baseline assessment. Measures to be delivered at this assessment point are outlined in Table 1.

#### Stage 6 - Post-intervention assessment and follow-up

All participants will be followed up at post-intervention and 6 and 12 months following the completion of treatment, using the assessment battery outlined in Table 1 and described below. In addition, as noted earlier, families in the waitlist condition will be re-assessed following completion of the 10-week monitoring period. The Research Assistants involved in conducting pre-treatment and follow-up assessments will be blind to participants' treatment condition.

This study will aim to recruit a total of 140 participants (approximately 45 in each condition). Recruitment will be carried out over an 18-24 month period at three hospital sites. A comparison of the two active treatments to the waitlist control condition will establish the basic efficacy of both CF-CBT and FF-CBT. A comparison of the two active treatment conditions will test whether the efficacy of CBT for PTSD following accidental injury can be enhanced with parent involvement. Importantly, the battery of questionnaires used in this study will allow assessment of whether the active treatment conditions are associated with improvements in psychological symptoms as well as health-related quality of life. Further, the design of the study will allow for an examination of improvements and maintenance of gains (for the active treatments) over a 12-month follow-up period.

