### The importance of early intervention

Another issue which requires attention concerns the optimal timing for delivery of CBT interventions for childhood PTSD. In terms of the course of PTSD in children and adolescents, the current adult literature and the few existing prospective studies of children presenting with PTSD suggest that a steep decline in PTSD rates may be expected within the first year following the traumatic event [26-28]. However, a significant proportion of children who initially present with PTSD following a traumatic event are highly likely to continue to experience PTSD over the long-term if they do not receive treatment. There is then a fine balance to be struck between the need to provide early intervention in order to prevent the development of emotional and behavioural problems after trauma, and the need to avoid treating young people who do not need treatment and would instead recover on their own.

Strategies for identifying those most at risk for the development or continuation of poor psychological adjustment after trauma may represent the best way forward. Kenardy and colleagues [10] reported that early self-reported symptoms of PTSD in children injured in accidents (measured at 1-2 weeks post-injury) predicted the presence of PTSD symptoms at 4-6 weeks and 6 months post-injury. Using a specially developed scale (the Child Trauma Screening Questionnaire; CTSQ), the diagnosis of 91% of children was correctly predicted in this study. Thus, it is possible to identify those children most likely to be 'at-risk' of PTSD diagnosis within the first two weeks following the injury. Moreover, it is proposed that early intervention targeted at children who demonstrate the presence of PTSD symptoms at 4-6 weeks, will be effective in significantly reducing the longer-term prevalence of PTSD and anxiety disorder symptoms.

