## Methods/Design

### Design of the Trial

This study is designed as a three arm randomised controlled trial with two active interventions ('*child-focused' *and *'family-focused'*) and one comparison (*'waitlist'*) condition. The study will be conducted across 3 hospitals in Australia, The Royal Children's Hospital (RCH) in Brisbane, The Mater Children's Hospital (MCH) in Brisbane and the Women's and Children's Royal Hospital (WCH) Adelaide. There will be six measurement occasions: screening at 1-2 weeks post-hospital admission, baseline, 4-weeks post-baseline, post-intervention, and follow-ups at 6 and 12 months after the post-intervention assessment. A half crossover design will be used to allow baseline and post-test comparisons between the two active treatment conditions and waitlist control group on primary and secondary outcome measures, as well as increasing the sample size for the final evaluation at follow-up. Thus, all children in the waitlist condition will be randomly allocated to one of the two active treatment conditions following their initial waiting period.

This study was granted ethical approval by the University of Queensland Human Research Ethics Committee (protocol number2008002119), the Royal Children's Hospital (Brisbane) Children's Health Service District Ethics Committee (protocol number HREC/09/QRCH/41), The Mater Health Services (Brisbane) Human Research Ethics Committee (protocol number 1305C) and the Children Youth and Women's Health Services (Adelaide) Human Research Ethics Committee (protocol number REC2149/2/2112). The study is funded by an NHMRC Project Grant (569660). The measures to be administered at each time point are listed in Table 1.

**Table 1 T1:** Measures to be administered at each measurement occasion

Measure	Screening	Baseline	4-weeks post-baseline	Post-test	6-month	12-month
Demographics	X	X				
Child Trauma Screening Questionnaire	X	X	X	X	X	X
Heart-rate	X					
Injury severity	X					
Clinician Administered PTSD Scale-Child and Adolescent Version		X	X	X	X	X
Faces Pain Scale		X		X	X	X
Child PTSD Symptom Scale		X	X	X	X	X
Child Depression Inventory-Revised		X		X	X	X
Spence Children's Anxiety Scale		X		X	X	X
Pediatric Quality of Life Scale - Child version		X		X	X	X
Child Behavior Checklist		X		X	X	X
State Trait Anxiety Inventory		X		X	X	X
Pediatric Quality of Life Scale - Parent version		X		X	X	X
Depression, Anxiety and Stress Scale		X		X	X	X
Posttraumatic stress Diagnostic Scale		X	X	X	X	X

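### Post-test follows each arm's own end of treatment, about 4 weeks later after baseline in FF-CBT than in CF-CBT, so the powered contrast mixes parent involvement with extra time for natural recovery

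*Protocol article*

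**What the plan says.** Under Stage 6, "All participants will be followed up at post-intervention and 6 and 12 months following the completion of treatment". The Design of the Trial section likewise places "follow-ups at 6 and 12 months after the post-intervention assessment", so any offset between arms at post-test carries into both later visits.

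The arms differ in length. In The Interventions, "The child/adolescent program consists of six sessions", which is all that CF-CBT receives, and "The parent program consists of four sessions", which FF-CBT adds. In FF-CBT, "the parent and child programs will be delivered consecutively, with parents completing parent sessions first". The weekly frequency appears only in the eligibility table: "Family must live within 200 km's or be willing to travel for weekly therapy sessions". Stage 5 agrees with it, since the parent program is to take four weeks. Random Allocation Procedure starts each allocated condition one week after randomisation. For the waitlist, Stage 4 says: "Participants in the WLC will be randomly assigned to one of the two active treatment conditions after 10 weeks", with a reassessment at that time.

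On natural course, the Background says that "a steep decline in PTSD rates may be expected within the first year following the traumatic event". Baseline is about 4-6 weeks after admission (Stage 3). Statistical Considerations tests diagnostic status by chi-square at each assessment occasion and analyses continuous outcomes with linear mixed models. Sample Size and Power Calculations says the trial is powered on FF-CBT versus CF-CBT.

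**The concern.** A comparison at nominal post-test is fair if the arms are assessed at the same time after baseline, or if symptoms would be stable without treatment. Here the arms have different lengths, and the article itself expects PTSD rates to fall during the first year, in which every post-test lies. A child in FF-CBT has about four more weeks to recover unaided before being assessed than a child in CF-CBT.

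Stage 6 says the comparison of the active arms is to show whether parent involvement enhances CBT. Calendar time is not parent involvement, yet as written the two cannot be separated, and the bias runs towards the hypothesis that FF-CBT is superior. For CF-CBT versus waitlist it runs the other way and could hide part of a real benefit.

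The article recognises the principle elsewhere. Stage 5 puts the 4-week assessment on one clock in all arms so that they can be compared. That visit cannot stand in for the post-test, because FF-CBT children have not yet begun the child program.

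**Working it through.** **Timeline (weeks after baseline).** The article states no post-test week for the active arms, so there is no figure to reproduce. Week of post-test = start lag + number of weekly sessions. Three readings of the one-week lag are possible:

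- No lag: CF-CBT 6, FF-CBT 4 + 6 = 10, waitlist 10.
- Lag in the active arms only: CF-CBT 1 + 6 = 7, FF-CBT 1 + 4 + 6 = 11, waitlist 10.
- Lag in all arms: CF-CBT 7, FF-CBT 11, waitlist 1 + 10 = 11.

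FF-CBT minus CF-CBT is 4 weeks on every reading, because the lag cancels. Waitlist minus CF-CBT is 3-4 weeks. FF-CBT minus waitlist is 0-1 week.

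**Size of the gap if neither treatment works.** The recovery rate is an assumption: a proportion R of 30%, 50% or 70% remits untreated over B = 52 or 26 weeks after baseline, at constant hazard. Then h = -ln(1 - R)/B, and remission by week t is 1 - exp(-h t). Example, R = 50% and B = 52: h = 0.6931/52 = 0.01333; week 7 gives 8.9%, week 11 gives 13.6%, a difference of 4.7 points.

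The rejection rate is that of the uncorrected two-sided 5% chi-square for FF-CBT versus CF-CBT, by exact enumeration of two binomials with 36 per arm (45 less 20% attrition).

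| Assumed R over B | CF, week 7 | Waitlist, week 10 | FF, week 11 | FF - CF | Waitlist - CF | Rejection |
|---|---|---|---|---|---|---|
| 30% / 52 wk | 4.7% | 6.6% | 7.3% | 2.6 | 1.9 | 6.9% |
| 50% / 52 wk | 8.9% | 12.5% | 13.6% | 4.7 | 3.6 | 10.5% |
| 70% / 52 wk | 15.0% | 20.7% | 22.5% | 7.5 | 5.7 | 12.7% |
| 30% / 26 wk | 9.2% | 12.8% | 14.0% | 4.9 | 3.7 | 10.6% |
| 50% / 26 wk | 17.0% | 23.4% | 25.4% | 8.4 | 6.4 | 13.6% |
| 70% / 26 wk | 27.7% | 37.1% | 39.9% | 12.2 | 9.4 | 20.3% |

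If the waitlist is at week 11, its gap to CF-CBT equals the FF - CF column. A continuity correction lowers the three 26-week rejection rates to 4.1%, 8.7% and 13.4%.

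**Size if both treatments work equally well.** Take 69% diagnosis-free in CF-CBT. This is an assumption, borrowed from the child-focused arm of the anxiety trial cited in the Background. Let the remaining 31% go on remitting at hazard h for four more weeks: FF = 1 - 0.31 exp(-4h). This gives 69.8%, 70.6% and 71.7% on the 52-week hazards, and 70.7%, 72.1% and 74.2% on the 26-week hazards. Rejection is 5.4%, 5.5%, 6.0% and 5.5%, 6.2%, 8.0%. With no timing gap the same test rejects in 5.3%.

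**Follow-up.** Adding 26 and 52 weeks to weeks 7 and 11 compares weeks 33 with 37 and 59 with 63. With no treatment effect, the FF - CF offset is 2.2-4.2 points at 6 months and 1.1-2.4 points at 12 months across the six scenarios.

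**The case against.** **Assessing at the end of treatment is a common choice.** The hypotheses concern change after treatment and maintenance of gains, for which equal time since the last session is natural. A common week exchanges unequal time since injury for unequal time since therapy ended. This is a fair cost, but it does not remove the bias in the contrast that the trial is powered on.

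**Natural recovery may be slow in this sample.** The children screened positive at 1-2 weeks and still met criteria at 4-6 weeks, and the sentence after the one on steep decline says many untreated children will keep PTSD. A reader might infer that the article predicts a steep fall in just the weeks between the two post-tests. It speaks only of the first year, so the 52-week scenarios are closer to its wording.

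**The error inflation is easily overstated.** A reader might take a false-positive rate of up to 20% as the finding. That needs two ineffective treatments and 70% remission within 26 weeks, whereas the article expects CBT to have large effects against control. Nor should the gaps be set against a planned 23-point difference: 92% versus 69% is a 3-year result in another population, and the stated planning effect is w = 0.50.

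**Not every contrast is affected.** FF-CBT versus waitlist is aligned to within a week, and the bias in CF-CBT versus waitlist is conservative.

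**The mixed model might use actual time.** Time coding may be settled in an analysis plan that is not shown, so its absence here is not an error. The chi-square tests, however, are specified by occasion, and they cannot use elapsed time.

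**Conclusion.** The concern holds at moderate severity. The 4-week FF-CF offset follows from the article's session counts and weekly frequency, whichever way the start lag is read. Its direction favours the hypothesis in the powered contrast and works against CF-CBT in its comparison with the waitlist.

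Its size depends on a recovery rate that the article does not give. Under the assumed range, timing alone is worth 2.6-12.2 points between FF-CBT and CF-CBT if neither treatment works, with rejection of about 7-13% (52-week remission) or 11-20% (26-week remission). If both work equally well, rejection is about 5.4-8.0%, little above nominal. At follow-up the offset shrinks to about 1-4 points. The documents do not support the inference that the trial's main result would be spurious, or that all three contrasts are compromised.

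**What to change.** Set one post-test week for all three arms, counted from baseline or randomisation, no earlier than completion of the FF-CBT programme and identical to the waitlist reassessment. Count the 6- and 12-month visits from that same anchor. State whether the waitlist's 10 weeks run from randomisation or from the start one week later. On a single clock they already coincide with the end of FF-CBT, so the change concerns assessment timing and leaves the therapy as it is.

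For children already assessed, enter actual weeks since baseline in the mixed model and report the arm contrasts at a common week. For diagnostic status, add a time-adjusted model as a sensitivity analysis beside the chi-square.

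The cost is a visit-window amendment and one more time variable. The downside is that CF-CBT children are assessed about four weeks after their last session rather than at once, which the report should say when it discusses maintenance of gains.

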### Study Hypotheses

It is hypothesized that:

• Following treatment, compared to participants in the WLC, participants in both active treatment conditions will demonstrate significantly greater reductions in child trauma, anxiety and depressive symptoms, significantly higher ratings on a health-related quality of life measure and significantly reduced ratings of functional impairment.

• Compared to participants in the CF-CBT treatment condition, participants in the FF-CBT treatment condition will demonstrate significantly greater reductions in child trauma, anxiety and depressive symptoms, significantly higher ratings on a health-related quality of life measure, significantly reduced ratings of functional impairment, significantly greater reductions in parental anxiety, trauma and depressive symptoms and significantly increased parental perception of their own ability to support their child.

• These treatment gains (and differences) will be maintained over 6- and 12-month follow-up.

### Primary Outcome Measure

The primary outcome measures will involve an assessment of posttraumatic stress symptoms. Diagnostic status, symptom severity and associated disability/impairment will be assessed using the Clinician Administered PTSD Scale for Children [31].

### Secondary Outcome Measures

Secondary outcome measures include a variety of measures administered to assess child and parent outcomes.

Child secondary outcomes include: trauma symptoms/risk indicators, assessed using the Child Trauma Screening Questionnaire [CTSQ; [10]]; PTSD symptoms, measured through the self-report Child PTSD Symptom Scale [CPSS; [32]]; anxiety, measured by the Spence Child Anxiety Scale [SCAS; [33]]; depression, measured by the Child Depression Inventory [CDI; [34]]; quality of life, measured through the Pediatric Quality of Life Inventory, Child and Parent Versions [PedsQL; [35]]; internalising and externalising symptoms, measured by the Child Behavior Checklist [CBCL; [36]]; intensity of children's pain, measured by the Faces Pain Scale - Revised [FPS; [37]].

Parent secondary outcomes include: parent PTSD symptoms, assessed through the self-report, Posttraumatic Stress Diagnostic Scale [PDS; [38]]; parental psychopathology, assessed by the Depression Anxiety and Stress Scale [DASS; [39]]; parental state and trait anxiety, measured by the State Trait Anxiety Inventory [STAI; [40]].

In addition, overall distress and improvement will also be assessed using a Global Assessment of Impairment/Improvement Scale developed by the authors.

